## Abstract

**Background:**

Ageing has become a worldwide reality and presents new challenges for the health-care system. Research has shown that potentially inappropriate prescribing, both potentially inappropriate medications and potentially prescribing omissions, is highly prevalent in older people, especially in the nursing home setting. The presence of potentially inappropriate medications/potentially prescribing omissions is associated with adverse drug events, hospitalisations, mortality and health-care costs. The Collaborative approach to Optimise MEdication use for Older people in Nursing homes (COME-ON) study aims to evaluate the effect of a complex, multifaceted intervention, including interdisciplinary case conferences, on the appropriateness of prescribing of medicines for older people in Belgian nursing homes.

**Methods/design:**

A multicentre cluster-controlled trial is set up in 63 Belgian nursing homes (30 intervention; 33 control). In each of these nursing homes, 35 residents (≥65 years) are selected for participation. The complex, multifaceted intervention comprises (i) health-care professional education and training, (ii) local concertation (discussion on the appropriate use of at least one medication class at the level of the nursing home) and (iii) repeated interdisciplinary case conferences between general practitioner, nurse and pharmacist to perform medication review for each included nursing home resident. The control group works as usual. The study period lasts 15 months. The primary outcome measures relate to the appropriateness of prescribing and are defined as (1) among residents who had at least one potentially inappropriate medication/potentially prescribing omission at baseline, the proportion of them for whom there is a decrease of at least one of these potentially inappropriate medications/potentially prescribing omissions at the end of study, and (2) among all residents, the proportion of them for whom at least one new potentially inappropriate medication/potentially prescribing omission is present at the end of the study, compared to baseline. The secondary outcome measures include individual components of appropriateness of prescribing, medication use, outcomes of the case conferences, clinical outcomes and costs. A process evaluation (focusing on implementation, causal mechanisms and contextual factors) will be conducted alongside the study.

**Discussion:**

The COME-ON study will contribute to a growing body of knowledge concerning the effect of complex interventions on the use of medicines in the nursing home setting, and on factors influencing their effect. The results will inform policymakers on strategies to implement in the near future.

**Trial registration:**

Current Controlled Trials ISRCTN66138978

## Background

Population ageing presents new challenges for the health-care system [1]; optimising medicines’ prescribing is a major aspect in this regard [2]. Many studies across different health-care settings have revealed a high prevalence of potentially inappropriate prescribing in people aged 65 and older [3–5]. The term ‘inappropriate prescribing’ encompasses three categories: overprescribing, referring to the prescription of a drug without a valid indication; misprescribing, referring to incorrectly prescribing a drug for a valid indication; and underprescribing, referring to the failure to prescribe indicated drugs [2]. The presence of inappropriate prescribing has been associated with adverse drug events (ADEs) [6], hospitalisations [6–10] and mortality [7].

Over the last years, explicit (criterion-based) and implicit (judgement-based) tools have been developed to identify inappropriate prescribing [2]. A European explicit tool that is currently widely used allows the identification of ‘potentially inappropriate medications’ or PIMs (i.e. events of overprescribing and misprescribing) on the basis of the Screening Tool of Older People’s Prescriptions (STOPP) criteria and ‘potentially prescribing omissions’ or PPOs (i.e. events of underprescribing) on the basis of the Screening Tool to Alert to Right Treatment (START) criteria [11]. A second widely used explicit tool is the American Beers list [12]. Beers criteria allow identification of PIMs but not PPOs [12].

The prevalence of inappropriate prescribing is particularly high in nursing homes (NHs). Over the past 10 years, several studies have been conducted to identify interventions that can increase appropriate prescribing in this specific setting. Different types of interventions have been tested: educational approaches; pharmacists’ medication reviews; multidisciplinary team approaches and the use of computerised decision support systems (CDSS) [13–18]. These interventions have been tested separately or in combination. Narrative and systematic reviews on this topic showed mixed results [13–18]. This lack of robust conclusions can partly be explained by variability in the intervention, in the outcomes measured [14, 17] and in the quality of the studies [18]. Authors’ conclusions in the different reviews are quite similar: some interventions led to the identification and resolution of drug-related problems (DRPs) [17], but there is no evidence of an effect of the interventions on resident-related outcomes, namely ADEs, hospital admissions and mortality [14, 17, 18] and few or no study assessed quality of life [17]. Authors suggested that a comprehensive approach, including more than one method to improve the quality of prescribing, is likely to be required [13, 15, 18, 19]. As health-care professionals (HCPs) receive little training in pharmacotherapy in older people during their basic education, Forsetlund et al. insisted that any intervention should imply some kind of education [18]. Currently, the right combination of interventions that can improve the quality of prescribing in the nursing home setting is not clear. Moreover, as pointed out by Sanford et al., there is a heterogeneity in the nursing home characteristics between countries (number of beds, funding, nursing home residents (NHRs), trained or untrained staff, visit of physicians,…); hence, generalisation across countries is limited [20].

As most of the interventions tested were complex and multifaceted, some authors pointed out the lack of studies that explored this ‘black box’ effect through a process evaluation to understand the contribution and impact of each component [17, 18].

In Belgium, 8.4 % of the 65+ [21] and 42 % of the 85+ live in a NH [22]. Each Belgian NH must appoint a coordinating physician, who is, together with the head nurse, responsible for the therapeutic policy of the NH. Medication-related tasks include organising medication management in collaboration with pharmacists, developing and updating the medication formulary, organising training, etc. Each NHR can choose his/her general practitioner (GP); consequently, the number of visiting GPs is unrestricted. Furthermore, the GP has a total freedom of diagnostic and therapeutic strategies, although he is stimulated to follow the therapeutic policy of the NH. The delivery of medication is performed by pharmacies, either hospital pharmacies or community pharmacies. The NH is in charge of the choice of the delivering pharmacy.

A study conducted in Belgian NHs in 2006 found that the median number of chronic medications per patient was 8 (5–10) [22]. Fifty-three percent of residents received 5 to 9 chronic medications daily and 20.8 % had 10 to 14 chronic medications [22]. A particularly high consumption was observed for benzodiazepines and antipsychotics (68 %), laxatives (50 %) and antidepressants (46 %) [22]. In another Belgian study, more than 50 % of NHRs had at least one drug that could be stopped or modified according to the STOPP criteria, while for 30 % of the residents at least one drug was missing, based on the START criteria [23].

While policy approaches to improve the quality of drug prescribing in the nursing home setting have been adopted in several developed countries such as the USA, UK, Australia and New Zealand [24], no similar action has yet been set up in Belgium.

Given the high consumption of medications, the high prevalence of inappropriate use of medications, and the lack of structured interdisciplinary approaches in Belgian NHs, the Belgian National Institute for Health and Disability Insurance (NIHDI) launched a national call in 2013. The objective was to perform a national quality improvement pilot project, aiming at evaluating the effect of interdisciplinary collaboration on the appropriateness of use of medications by NHRs and developing recommendations to policymakers. This pilot project is the Collaborative approach to Optimise MEdication use for Older people in Nursing homes (COME-ON) study described hereafter.

### Objectives

The primary objective of the COME-ON study is to evaluate the effectiveness of a complex, multifaceted intervention on the appropriateness of prescribing for older people in Belgian NHs. General practitioners, coordinating physicians, nurses and pharmacists are involved in the COME-ON study. The intervention is built up from a number of components, mainly training, local concertation and interdisciplinary medication reviews during case conferences. These components may act both independently and inter-dependently. The intervention can therefore be considered as a complex intervention [25].

The secondary objectives are to evaluate the effect of the intervention on medication use, on resident outcomes in terms of hospital admissions and visits to the emergency department, and on costs. In addition, a process evaluation will be conducted to examine the extent to which the intervention is implemented as planned and to explore participants’ experiences regarding reasons of success or failure, barriers and facilitators.

The study development was informed by the Medical Research Council (MRC) guidance for developing and evaluating complex interventions [25]. The COME-ON study is built on (a) learning from previous research [15, 17, 18, 26], (b) focus groups with HCPs working in Belgian NHs to identify their needs with regard to optimization of medication use, and (c) a pilot study performed in four NHs spread in the three regions of Belgium. During this pilot study, the recruitment approach, the adequacy of research instruments and the feasibility and acceptability of interdisciplinary medication review were assessed.

## Methods/design

### Trial design

The COME-ON study is a multicentre, cluster, parallel-group controlled trial. Each NH represents one cluster. As the intervention is mainly provided at the level of HCPs, a cluster design was chosen to prevent contamination bias. The study design was developed in accordance with the Consolidated Standards of Reporting Trials (CONSORT) statement extension to cluster RCTs [27].

### Participating nursing homes (clusters)

In the summer of 2013, a national call addressed to all Belgian NHs was launched by NIHDI. Nursing homes with at least 35 residents were eligible to participate. For each NH willing to participate, the management board, coordinating physician and delivering pharmacist were asked to complete and sign an application file with descriptive data relative to the NH, to the residents and to the local medication management process. Each coordinating physician, pharmacist and management board could not be involved in more than one application (to maximise variability in the sample and to prevent contamination bias). In total, 72 NHs applied. After exclusion of duplicates (i.e. two or more applications with the same pharmacist, the same coordinating physician and/or the same management board), a final list of 63 NHs was obtained (Fig. 1).

**Fig. 1 Fig1:**
[figure not shown]
COME-ON study flowchart

### Allocation

Nursing homes were stratified by (a) province/region, (b) experience with multidisciplinary case conferences (as reported in the application file) and (c) type of medication delivery (by a hospital pharmacy or by one or more community pharmacies). Factors (b) and (c) were considered to be possibly significant covariates. Geographical location (factor a) was taken into account because the funding body (NIHDI), requested that (i) at least one NH from each province/region was given the opportunity to implement the intervention and (ii) the number of NHs allocated to each group was balanced per province/region.

In 4 of the 10 Belgian regions/provinces, only one NH applied. These 4 NHs were therefore immediately assigned to the intervention group. The characteristics of the other 59 NHs with regard to location (province/region), experience with case conferences and type of delivering pharmacy, were entered into Statistical Package for the Social Sciences (SPSS; version 22). This programme generated a series of blocks for each stratum and allocated NHs to control or intervention group randomly within each block. Allocation was performed by an independent researcher blinded to the identification of the NHs and not involved in the recruitment of NHs or residents. Thirty NHs were allocated to the intervention group (as stipulated by NIHDI) and 33 to the control group. Because of the nature of the intervention, it was not possible to blind NHs or HCPs to the intervention.

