### Data analysis

#### Quantitative analysis

Data from the trial will be analysed and reported in accordance with the CONSORT criteria. The baseline characteristics will be reported as mean (± standard deviation) or median (and P25; P75) values for continuous variables and as counts (percent) for categorical variables. Descriptive statistics will be used to evaluate differences between intervention and control group on baseline characteristics at the resident, physician and nursing home level. Continuous variables will be compared using Student *T* test or Wilcoxon rank-sum test for clustered data, as appropriate. Categorical variables will be compared using adjusted chi-square test for clustered data.

To assess the impact of the intervention on the primary outcomes, logistic regression will take into account the complex design issues of the study (clustering, stratification). A multivariable model will be built to adjust the analysis for potential confounders, i.e. the number of PIMs/PPOs at baseline per resident and other baseline characteristics of residents, GPs and NHs. The analysis will be conducted using the intent-to-treat analysis, i.e. all residents will be analysed as randomised. A per protocol analysis will also be performed as a secondary analysis.

The impact of the complex intervention on the secondary outcome measures will be assessed using descriptive data and in some cases, using appropriate statistical evaluation.

Data analysis will be performed using R software (Free Software Foundation, Inc., Boston, MA, USA). A *p* value <0.05 will be considered statistically significant.

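### Four of the 30 intervention homes were assigned by rule, so only 59 homes (26 vs 33) were randomised and the statement that all residents are analysed as randomised is wrong for them

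*Protocol article*

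**What the plan says.** The section on participating nursing homes reports that, after removal of duplicate applications, "a final list of 63 NHs was obtained". The Allocation section names province or region as a stratification factor and gives the funder's reason, namely that "at least one NH from each province/region was given the opportunity to implement the intervention". It continues: "In 4 of the 10 Belgian regions/provinces, only one NH applied". The consequence is stated openly: "These 4 NHs were therefore immediately assigned to the intervention group". Random allocation in blocks within strata was then applied only to the remainder: "The characteristics of the other 59 NHs with regard to location (province/region), experience with case conferences and type of delivering pharmacy, were entered into" the software. The result was: "Thirty NHs were allocated to the intervention group (as stipulated by NIHDI) and 33 to the control group".

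The Quantitative analysis section defines the primary analysis: "The analysis will be conducted using the intent-to-treat analysis, i.e. all residents will be analysed as randomised". The logistic model is to account for clustering and stratification and to adjust for baseline characteristics, including each resident's baseline number of PIMs/PPOs. The only other analysis set named is per protocol. The four directly assigned homes are not mentioned again, and they are not among the three limitations listed in the Discussion.

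**The concern.** The Allocation and Quantitative analysis sections do not agree. One says that four homes were never randomised; the other says that every resident is analysed according to randomisation. This is a statement about the primary analysis set that is untrue for part of that set, which is different from a detail left for the analysis plan.

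The four homes also differ in kind from the others. Each was the sole applicant in its province or region, so arm and province coincide there completely, and all four can enter only one side of the comparison. As the text stands, a report could present the estimate from 63 homes as a randomised comparison when part of the intervention arm has no randomised counterpart.

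**Working it through.** **Counts** (Allocation; Participating nursing homes)

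- Randomised homes: 63 − 4 = 59.
- Randomised to intervention: 30 − 4 = 26. Randomised to control: 33. Check: 26 + 33 = 59.
- Directly assigned share: 4/30 = 13.3% of intervention homes and 4/63 = 6.3% of all homes. At the planning cluster size of 30, that is 120 of 900 intervention residents.

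**What the four homes contribute under each model.** Province is a stratification factor, and the article says stratification is taken into account without saying how.

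- Province as a fixed factor: each of the four provinces holds one home in one arm. Its province term absorbs that home's result, and the home adds nothing to the treatment contrast.
- Province omitted, pooled or random: the home is compared with control homes in other provinces. That comparison is not randomised.

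**Possible shift in the second case.** The documents give no between-province difference, so one is assumed. With homes of equal size, if the 26 randomised intervention homes have rate p and the four homes have rate p + d, the arm rate is (26p + 4(p + d))/30 = p + 4d/30.

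| Assumed d (points) | Shift = 4d/30 (points) | Share of the 20-point effect, outcome 1 | Share of the 10-point effect, outcome 2 |
|---|---|---|---|
| 5 | 0.7 | 3% | 7% |
| 10 | 1.3 | 7% | 13% |

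On outcome 2 (at least one new PIM/PPO), Sample size plans 20% in control and 10% in intervention. A lower rate favours the intervention, and a rate of 10% can fall by at most 10 points. The largest favourable shift is therefore 10 × 4/30 = 1.3 points. A larger shift would require the four homes to do worse than the others, which moves the estimate towards no effect.

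**The plan's own sample size.** Inputs from Sample size: two-sided 5% (sidedness assumed), 80% power, cluster size 30, 22% dropout, ICC 0.05, design effect 1 + 0.05 × 29 = 2.45. For outcome 2, the two-proportion formula gives 199 per arm with pooled variance and 196.2 with unpooled. Total: 2 × 199 × 2.45/0.78 = 1250, or 2 × 196.2 × 2.45/0.78 = 1233, against the stated 1223. The stated figure is reproduced within 3%.

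**Cost of using 59 homes.**

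- Residents: 63 × 30 = 1890 becomes 59 × 30 = 1770, a loss of 120 (6.3%). The stated requirement of 1223 is still met.
- Power for 20% vs 10%, from Φ[(0.10 − 1.96·SE₀)/SE₁], where SE₀ is the pooled and SE₁ the unpooled standard error, on effective sizes of homes × residents/design effect.
- With dropout applied (30 × 0.78 = 23.4 residents per home) and the design effect kept at 2.45: control 33 × 23.4/2.45 = 315.2; intervention 30 × 23.4/2.45 = 286.5, or 26 × 23.4/2.45 = 248.3. Power goes from 93.1% to 91.1%.
- With 30 analysed residents per home: control 404.1; intervention 367.3, or 318.4. Power goes from 97.4% to 96.4%.
- At higher ICCs with 30 per home: 87.0% to 84.1% at 0.10, 64.3% to 60.2% at 0.20, and 33.2% to 30.2% at 0.5. The loss is at most about 4 points. The low power at the larger ICCs is present with all 63 homes and is not caused by the exclusion.

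**The case against.** The best defence is that nothing is concealed. The article states the rule, its reason and the number of homes, and it describes the study as a controlled trial. The four homes were placed by a fixed rule and not chosen on prognosis. Both primary outcomes are changes from each resident's own baseline, and the model adjusts for baseline PIMs/PPOs and home characteristics, so stable regional differences in prescribing level are partly removed. How province enters the model is normally left to an analysis plan, which is not shown. Since the funder wanted every province to have the opportunity and the results are meant for national policy, a primary analysis of all 63 homes can be defended.

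Most of this stands, and it limits the point. Disclosure of the allocation does not make the analysis statement true, and adjustment does not create a randomised comparison where there was none. Silence on the form of the province term is not counted as a fault here.

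A reader might go further and infer that any regional difference will be credited to the intervention. The documents do not support that. The other provinces were randomised in blocks within strata, so only the deviation of the four homes can enter, diluted by 4/30, and only if province is not a fixed factor. A reader might also take differences of 20 or 30 points and infer shifts of 2.7 or 4.0 points in the intervention's favour. On outcome 2 that is impossible, because the planned 10% rate cannot fall that far.

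**Conclusion.** The point holds as a wrong statement about the primary analysis. Only 59 of 63 homes were randomised, and the intent-to-treat sentence is untrue for 13% of intervention clusters. Depending on how province is modelled, those homes either carry no information on the treatment effect or bring in a non-randomised comparison on one side.

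Whether there is bias, and how large, is unknown. The range of 0.7 to 1.3 points rests on an assumed difference of 5 to 10 points, equal home sizes and no adjustment. The cap of about 1.3 points on a favourable shift applies to outcome 2 and assumes the planned 10% rate in the other intervention homes. The documents do not show that the trial result is biased. Nor do they support reading the smaller randomised sample as a power problem: at an ICC of 0.05, power on outcome 2 stays above 90% with 59 homes.

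**What to change.** Base the primary comparison for both primary outcomes on the 59 randomised homes (26 vs 33), with the stratification factors in the model. Report all 63 homes, described as analysed *as allocated*, as a sensitivity analysis. If the sponsor prefers to keep 63 homes as primary because of the national remit, the minimum is to pre-specify the 59-home analysis. In either case, replace the phrase "all residents will be analysed as randomised" with wording that is true of the set used. The four directly assigned homes can still serve the process evaluation and the description of implementation.

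No new data are needed. Making the 59 homes primary costs about 6% of residents (1770 instead of 1890 at 30 per home, still above 1223) and 1 to 2 points of power on outcome 2 at an ICC of 0.05. The sensitivity-only version costs only wording and one extra analysis.

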### Nursing homes residents

Residents were considered eligible if they were aged 65 years or older and were under the care of a participating GP. Before the study started, the coordinating physician contacted all GPs who had at least one resident in the NH to ask for their willingness to participate in the study. Residents receiving palliative care (according to the GP’s evaluation) and residents in subacute care/rehabilitation were excluded.

